### Sample analysis

Stool will be analysed by the APC Microbiome Ireland laboratory. Stool samples will be stored at −80°C. The extraction of DNA from faecal matter will be conducted using the QIAmp Fast DNA Stool Mini Kit (QIAGEN, Manchester, UK), which includes an initial bead-beating step in the process.^68^ Microbiome analysis of stool will be performed using shotgun metagenomics sequencing. Initially, the DNA will undergo fragmentation, where it is sheared into fragments of approximately 400–600 bp and tagged with Illumina adaptor sequences. Subsequently, an indexing PCR will be carried out to uniquely index each sample, facilitating the pooling of samples on a single-flow cell and subsequent bioinformatic demultiplexing. Following Illumina Nextera XT protocols, PCR amplicons will be cleaned and normalised. To ensure an even distribution of samples for pooling, qPCR will be conducted. All metagenomic samples will be sequenced on the Illumina NextSeq platform. Raw reads will be filtered based on quality, quantity and length of reads, as well as the removal of human reads. Stool microbiota composition and functionality will be analysed using state-of-the-art methods. Faecal SCFAs will be measured in all study participants as SCFAs have previously been reported to have a protective effect against developing autoimmunity.^69^,^72^ Faecal SCFAs will be analysed by gas chromatography flame ionisation detection using a Varian 3800 GC system, fitted with a DB-FFAP column (30 m L × 0.32 mm ID × 0.25 µm df; Agilent, California, USA) and a flame ionisation detector. Urine for metabolomics will be stored at −80°C and later analysed for untargeted metabolomics at University College Cork. Mass spectrometry methods for biomarker identification, followed by targeted/hypothesis-driven metabolomics methods for biomarker verification, will be conducted.

Statistical instruments for the analysis of microbiome data sets are continually being updated, and we will use the latest methodology available. Part of the faecal samples will be grown for analyses of culturable bacterial strains.

Serum for diabetes autoantibodies will be analysed by Exeter Clinical Laboratory in the UK. Serum for HLA-typing will be analysed at the National Blood Centre, [name]. Serum for HbA1C measurement, glucose and C peptide analysis will be analysed at CUH. Samples will be stored securely in a UCC monitored biobank until transfer for analytics to the relevant laboratory.

### Bioinformatics and statistical analysis

#### Demographic and clinical data

Demographic and clinical data, as well as laboratory information, will be subjected to a normality test using the Shapiro-Wilk test. Descriptive statistics will be employed to characterise data that conform to a normal distribution and will be presented as mean ± SD. Continuous data lacking a normal distribution will be presented using the median and IQRs. Categorical variables will be conveyed as counts and percentages. Group comparisons will involve χ^2^ tests for categorical variables and independent-sample Student’s t-tests for continuous variables meeting the normal distribution criteria. In the case of variables that do not adhere to a normal distribution, the Mann-Whitney U test will be employed.

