## Methods and analysis

This study will recruit 50 children at the time of diagnosis and 50 unaffected sibling controls and will employ a prospective cohort study methodology to investigate the faecal microbiome of children with newly diagnosed T1D in the first year of diagnosis. All children with newly diagnosed T1D will be assessed for eligibility for enrolment in this study. Inclusion and exclusion criteria are outlined separately in the recruitment strategy outline. Parents of eligible cases and controls will be approached for consent. If a case does not have siblings, they will still be eligible for recruitment. If a case has multiple siblings, more than one sibling can be recruited as a control. Recruitment will be conducted over a 1-year period. Consent for enrolment for both cases and controls will be obtained during the first hospital visit on diagnosis of the index case. The study started in October 2023 and is planned to finish by September 2026.

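### A Shapiro-Wilk result picks the summary and the test, and unequal variances are never addressed, so the 5% error rate is not held when group sizes and variances both differ

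*Protocol article*

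**What the plan says.** The rule is in the protocol article under Bioinformatics and statistical analysis, Demographic and clinical data. It covers demographic, clinical and laboratory variables, which "will be subjected to a normality test using the Shapiro-Wilk test".

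The outcome of that test fixes two things:

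- **Summary.** Descriptive statistics are for "data that conform to a normal distribution and will be presented as mean ± SD". Otherwise, "Continuous data lacking a normal distribution will be presented using the median and IQRs".
- **Test.** The plan uses "independent-sample Student’s t-tests for continuous variables meeting the normal distribution criteria". The alternative is: "In the case of variables that do not adhere to a normal distribution, the Mann-Whitney U test will be employed".

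The section gives no threshold for the pre-test. It does not say whether the pre-test is run within each group or on the pooled data, and it mentions neither a variance check nor Welch's test. On group sizes, Methods and analysis states: "This study will recruit 50 children at the time of diagnosis and 50 unaffected sibling controls". The same section admits cases without siblings and allows several siblings per case. Objectives and outcomes lists DKA versus no DKA among the secondary comparisons, with no expected split.

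**The concern.** Student's t-test in its usual form pools the two variances. Its error rate therefore depends on equal variances as soon as the groups differ in size. The Shapiro-Wilk step looks only at shape, so a variable can pass it and still be analysed with the wrong standard error. The DKA comparison is not balanced by design, and case and control numbers can drift from 50 and 50. A clinical or laboratory comparison made on those groups could then be too liberal or too conservative, depending on which group is more variable.

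The second issue is separate and needs no difference in variance. A normality test has little power in small samples and high power in large ones. Sample size can then decide whether a skewed laboratory value is reported as a mean or as a median, and whether means or ranks are compared. Results for one variable would not be comparable across groups of different size.

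**Working it through.** **Inputs from the article.** The pre-test and the two tests are as above. Planned sizes are 50 cases and 50 controls, and DKA status is compared within about 50 cases.

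**Assumptions (the article gives none of these).** Two-sided 5% level; Shapiro-Wilk threshold 5%; DKA splits of 20/30, 15/35 and 10/40; case/control drift to 40/60; SD ratios of 1, 1.5 and 2. There is no stated figure to reproduce.

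**Step 1: why the pooled t-test goes wrong.** The true variance of the mean difference is σ₁²/n₁ + σ₂²/n₂. The pooled test estimates s²ₚ(1/n₁ + 1/n₂), where s²ₚ has expectation [(n₁−1)σ₁² + (n₂−1)σ₂²]/(n₁+n₂−2). With R the ratio of true to estimated variance, the error rate is roughly 2[1 − Φ(1.96/√R)].

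- **15 v 35, SDs 2 and 1.** True: 4/15 + 1/35 = 0.295. Pooled: (14×4 + 34×1)/48 = 1.875, times (1/15 + 1/35) = 0.0952, gives 0.179. R = 1.65, √R = 1.286, error about 12.7%.
- **15 v 35, SDs 1 and 2.** True: 1/15 + 4/35 = 0.181. Pooled: (14×1 + 34×4)/48 = 3.125, times 0.0952, gives 0.298. R = 0.608, √R = 0.780, error about 1.2%.
- **50 v 50, SDs 2 and 1.** True: 4/50 + 1/50 = 0.10. Pooled: 2.5 × 2/50 = 0.10. R = 1, error 5%.
- **Equal SDs, any sizes.** R = 1, error 5%.

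**Step 2: the full two-stage rule, simulated.** Normal data, equal means, 8,000 data sets per setting (Monte Carlo standard error about 0.25 points at 5%). Each cell gives the type I error with the pre-test applied per group / to the pooled sample.

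| Sizes | Smaller group has larger SD, ratio 1.5 | Smaller group has larger SD, ratio 2 | Larger group has larger SD, ratio 2 |
|---|---|---|---|
| 40/60 | 7.5% / 6.5% | 8.3% / 7.4% | 2.8% / 3.0% |
| 20/30 | 7.5% / 6.3% | 8.8% / 7.1% | 3.1% / 3.2% |
| 15/35 | 9.6% / 8.8% | 12.7% / 10.4% | 1.6% / 1.3% |
| 10/40 | 12.0% / 11.4% | 18.3% / 14.3% | 0.7% / 0.7% |

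Welch's test on the same data stayed between 4.4% and 5.6% in every scenario run.

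**Step 3: where the rule holds.** With unequal sizes but equal SDs and the same shape (10/40 to 40/60; normal, gamma or log-normal), it gives 4.4% to 5.8%. With 50/50 and normal data it gives 5.1% at SD ratio 1 and 4.8% to 5.7% at SD ratio 2.

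**Step 4: which component is at fault.** At 15/35 with SD ratio 2 and the larger SD in the smaller group, Student's t with no pre-test gives 12.8%, against 12.7% for the two-stage rule with a per-group pre-test. The pre-test neither causes nor cures the problem. Mann-Whitney alone gives 9.1%, so moving to it is no remedy either.

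**Step 5: sample size and the summary.** For one log-normal variable (log-SD 0.6), Shapiro-Wilk at 5% passes about 68% of samples at n=10, 35% at n=20 and 2% at n=50. The variable is unchanged; only n differs.

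**The case against.** The strongest points on the other side are these.

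- **The inputs are assumed.** The article gives no DKA split, SDs or significance level, and the largest figures combine a very uneven split with a doubled SD in the unfavourable direction. This stands, and it is why both directions and a range are shown.
- **A reader might infer that unequal groups alone break the error rate, or that the Shapiro-Wilk step is what breaks it.** Neither is supported. Equal SDs keep about 5% at every split tried, and the planned 50/50 comparison keeps it with normal data. Deleting the pre-test while keeping Student's t would leave the error where it is.
- **A reader might also infer that the test will probably switch between subgroup and cohort.** That is not shown. If both groups must pass before a t-test is used, the log-normal variable above (log-SD 0.6) reaches a t-test in only about 4% to 6% of data sets at these splits. The section also does not say that the pre-test is repeated by subgroup or visit. What remains is that the summary of a single small group may differ from that of the full cohort.
- **The scope is narrow.** The DKA objectives are worded for the microbiome and metabolome, the sequencing workflow has its own section, and the study calls itself exploratory. This stands and limits the weight.
- **The detail may be in a fuller plan.** That would excuse silence. Here the article commits to a named test and a named selection rule, so the rule can be judged as written.

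**Conclusion.** The concern holds in a conditional form. The stated rule does not hold 5% when group sizes and variances both differ. At 15 v 35 and SD ratio 2 with normal data, the error is about 10-13% or about 1-2%, depending on which group is more variable, while Welch stays near 5%. The splits, SD ratios, 5% level and pre-test threshold are assumptions. The fault lies almost wholly in the equal-variance t-test.

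The dependence of the summary on sample size is a second, smaller fault that needs no assumption about variances. No primary or secondary objective is shown to rest on this rule. It is a change that should be made, of modest weight, because it affects clinical and laboratory comparisons in an exploratory study and not the sequencing analysis.

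**What to change.** In Demographic and clinical data:

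1. Replace Student's t-test with Welch's t-test, or a regression with robust standard errors, and report the difference with a 95% CI.
2. Set the scale, summary and test for each variable in advance instead of by a Shapiro-Wilk result: for example, a log scale for right-skewed laboratory values, and Mann-Whitney only for variables named beforehand. Use the same summary for a variable in every group and at every visit.

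The cost is about two sentences of wording, no extra data, and a negligible loss of power when variances are equal. The study is planned to run to September 2026, so the change can be recorded before the analysis.

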### Objectives and outcomes

The primary aim of this study is to describe the evolution of the microbiome and metabolome in children during their first year with stage 3 T1D, compared with their siblings without diabetes.

Secondary objectives and outcomes:

To establish if there are differences in the microbiome or metabolome of children who present in diabetic ketoacidosis (DKA) versus those who present without DKA.To establish if there are differences in the microbiome or metabolome in those presenting with mild, moderate or severe DKA.To establish if there is an association between the microbiome or metabolome and glycaemic control during the first year of diagnosis.To establish if there is an association between the microbiome or metabolome and beta cell reserve 1 year after T1D diagnosis.To establish if there is an association between the microbiome or metabolome at the time of T1D diagnosis and preceding hyperglycaemia.

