At each time point (0, 4, 8, 52 weeks), stool will be collected for microbiome analysis from all cases and controls (n=100). Urine for metabolomics will be collected from all study participants at the same time points. A food frequency questionnaire will be completed by all cases and controls at the first and fourth study visits (0 and 52 weeks, respectively). Clinical data, including insulin dosing, glycaemic control and blood results, will be documented at each visit for cases. Cases will be asked to participate in a mixed meal tolerance test (MMTT) at study visit four (52 weeks). This will quantify stimulated C peptide. This result will help to establish if there is a correlation between microbiome and metabolome evolution and beta cell reserve at 1 year. Shotgun metagenome sequencing will be conducted on faecal samples and urine metabolomic analysis will be employed to detect metabolic biomarkers. The study will explore the impact of the underlying diagnosis and environmental factors. The mode of delivery plays a crucial role in shaping the composition and function of the neonatal microbiome.^66 67^ Caesarean section delivery affects early microbiota transmission from mother to infant and the subsequent priming of the immune system, with delivery-dependent differences early in gut microbiota colonisation continuing through the first year of life.^66 67^ Due to this, we will record the mode of delivery in our data collection with ethical approval to access patient charts and will perform shotgun sequencing to compare cases with age-matched controls from 6 months onwards, should any become available.

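### The independent-sample tests named for demographic, clinical and laboratory data ignore that controls are siblings of the cases, so case-sibling comparisons run as written are conservative and lose power

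*Protocol article*

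**What the plan says.** The section *Demographic and clinical data* sets its own scope: "Demographic and clinical data, as well as laboratory information, will be subjected to a normality test using the Shapiro-Wilk test". Group comparisons there use χ² tests "for categorical variables and independent-sample Student’s t-tests for continuous variables meeting the normal distribution criteria". For the remaining continuous variables, "In the case of variables that do not adhere to a normal distribution, the Mann-Whitney U test will be employed". No other inferential tests are named in the article.

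The *Methods and analysis* section fixes who is compared: "This study will recruit 50 children at the time of diagnosis and 50 unaffected sibling controls". Family sizes may differ. On one side, "If a case does not have siblings, they will still be eligible for recruitment"; on the other, "If a case has multiple siblings, more than one sibling can be recruited as a control". The primary aim, under *Objectives and outcomes*, reads: "describe the evolution of the microbiome and metabolome in children during their first year with stage 3 T1D, compared with their siblings". No family term appears anywhere in the analysis text.

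**The concern.** Siblings share genes, household and diet, so their values are likely to be positively correlated. That is the usual reason for choosing sibling controls, and the article lists them among its strengths. An independent-sample test treats the case mean and the control mean as uncorrelated. It therefore leaves out the covariance that makes a sibling comparison precise, and where a family supplies several controls it also ignores the correlation among them.

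The variables exposed are those that the section covers and that both groups have: demographics, mode of delivery, HLA type, height and weight at visit 4, and the food frequency questionnaire. Faecal short-chain fatty acids are measured in all participants and would be added if they count as laboratory information, which the article does not settle. At stake is precision in a single-site study with about 50 children per group.

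**Working it through.** **Inputs.** From the article: 50 cases, 50 sibling controls, and none, one or several controls per family. The article gives no alpha, effect size or sibling correlation, and no power figure to reproduce. Assumed here: two-sided 0.05, a true difference of 0.5 SD, equal variances, and sibling correlation ρ of 0.1, 0.3 and 0.5, the same for case-sibling and sibling-sibling pairs. Values are in SD units, one per child.

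**Standard error that the independent test uses.** √(2/50) = 0.200. The test rejects when the difference exceeds 1.96 × 0.200 = 0.392. With ρ = 0, power is Φ((0.5 − 0.392)/0.200) = 70.5%, and nothing is lost.

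**True standard error, 50 one-to-one pairs.** Var(difference) = (2 − 2ρ)/50. Actual type I error = 2[1 − Φ(0.392/SE)]. Power of the independent test = Φ(0.108/SE). Power with the correct SE = Φ(0.5/SE − 1.96).

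| ρ | True SE | SE overstated by | Type I error | Power, independent test | Power, family accounted for |
|---|---|---|---|---|---|
| 0.1 | 0.190 | 1.05 | 3.9% | 71.5% | 75.0% |
| 0.3 | 0.167 | 1.20 | 1.9% | 74.1% | 84.8% |
| 0.5 | 0.141 | 1.41 | 0.6% | 77.7% | 94.2% |

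A simulation of 40,000 runs per setting agrees. Type I error of the independent t-test was 3.7%, 2.0% and 0.7%. Its power was 71.0%, 72.9% and 76.5%, against 73.7%, 83.4% and 93.5% for the paired test.

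**True standard error, mixed families.** As an illustration, take 15 cases with no sibling, 20 with one and 15 with two: 20 + 30 = 50 controls. The 15 two-sibling families raise the variance of the control mean to (50 + 30ρ)/2500 = (1 + 0.6ρ)/50. The 50 case-sibling pairs give a covariance of 50ρ/2500 = ρ/50. So Var(difference) = (1 + 1 + 0.6ρ − 2ρ)/50 = (2 − 1.4ρ)/50.

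| ρ | True SE | SE overstated by | Type I error | Power, independent test | Power, correct SE |
|---|---|---|---|---|---|
| 0.1 | 0.193 | 1.04 | 4.2% | 71% | 74% |
| 0.3 | 0.178 | 1.13 | 2.7% | 73% | 80% |
| 0.5 | 0.161 | 1.24 | 1.5% | 75% | 87% |

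The last column is for the plain difference in means.

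**Does the direction hold?** If 50 controls come m to a family, the control mean has variance (1 + (m − 1)ρ)/50 and the covariance is still ρ/50, so Var(difference) = (2 + (m − 3)ρ)/50. With m = 2 (25 families) this is (2 − ρ)/50, and type I error is 4.4%, 3.4% and 2.4%. The sign changes only if m exceeds 3, or if ρ is negative.

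**The case against.** The strongest reply concerns scope. The named tests sit under demographic and clinical data, while the primary aim concerns the microbiome and metabolome. *Microbiome analysis* is a separate section that names profiling tools only, and *Sample analysis* leaves the statistics for microbiome data to whatever methods are current. A reader might infer that change over the year will be t-tested, or that it is not tested at all. The article supports neither reading: it leaves the method open, and the detail may stand in an analysis plan that is not shown.

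A reader might also infer inflated false positives from treating the samples at 0, 4, 8 and 52 weeks as independent. The article nowhere says that visits will be pooled. Little of what this section clearly covers is repeated in both groups: serial clinical data are for cases only, and controls have one HbA1c, one height and weight, and the questionnaire twice.

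Further, the study calls itself exploratory, its main aim is to describe, and the error is conservative. The correlations are assumptions, and at 0.1 the loss is about 3.5 points of power. Comparisons among cases, such as DKA versus no DKA, involve unrelated children (unless two cases come from one family), so independent tests suit them.

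All of this stands, and it limits the point to case-sibling comparisons of the data that the section covers. It does not remove the point. There the article names specific tests, and they do not fit the sibling controls that it recruits. That is a conflict in the stated text, not a detail left to another document.

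**Conclusion.** The point holds in a limited form. For single-visit case-sibling comparisons of demographic, clinical and laboratory data, the named tests misstate the standard error and discard the benefit of sibling controls. With one-to-one pairs and an assumed correlation of 0.3 to 0.5, the standard error is overstated 1.20 to 1.41 times, and about 11 to 16 points of power at 0.5 SD are lost. With the illustrative mixed families the overstatement is 1.13 to 1.24 times. With no correlation nothing is lost.

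The consequence is missed differences, not spurious ones, provided that the sibling correlation is positive and controls are not concentrated at more than three per family. The wording should be corrected before analysis. The point does not by itself threaten the primary aim, whose method the article leaves open.

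**What to change.** In *Demographic and clinical data*, restrict the χ², Student's t and Mann-Whitney U tests to contrasts between unrelated cases, for example DKA versus no DKA. For any case-sibling comparison, specify a mixed model with a random intercept for family, or GEE clustered on family, in the form suited to a continuous or categorical variable. Where the same measure is repeated in both groups, add a random intercept for child and a group-by-visit term.

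A simple paired t-test is not a substitute, because it has no place for cases without a sibling or for families with several controls. The model keeps both. It would also help to say whether faecal short-chain fatty acids and urine metabolites count as laboratory information under this section.

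The cost is a few lines of wording and slightly more programming. No new data and no change to recruitment are needed.

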#### Microbiome analysis

Metagenomic shotgun sequencing data will be analysed using bioBakery suite of tools (https://huttenhower.sph.harvard.edu/biobakery_workflows/). Trimmed and human reads filtered using KneadData (Harvard School of Public Health, Boston, Massachusetts, USA) with the default parameters. Quality-controlled data will be taxonomically profiled at the species level with relative abundance by MetaPhlAn4. Functional profiling will be performed using HUMAnN3 (Harvard School of Public Health, Boston, Massachusetts, USA)^73^ and strain profiling using StrainPhlAn (University of Trento, Trento, Italy).^74^

#### Data collection and management

During the study, all data entered in the CRF will be pseudonymised with a unique identification code allocated at the time of enrolment into the study, and stored in a REDCap database. Identifiable data will be stored separately to this information. Only members of the research team will have access to these identifiers.

The electronic Investigator Site File will be maintained and updated as required during the study. Computers used to collate the data will have limited access measures by encryption codes, username and passwords. Access will be restricted to authorised study personnel only. All identifiable data will be kept for 10 years as per our university Code of Research Conduct. Clinical information will not be released without the written permission of the participant, except as necessary for monitoring, auditing or inspection by the relevant authorities. Published results will not contain any personal data that could allow identification of individual participants. All investigators and associated staff have completed good clinical practice in research training and will comply strictly with the requirements of the General Data Protection Regulation regarding the collection, storage, processing and disclosure of personal information and will uphold the Act’s core principles.

